### Study design

A randomized, controlled, three-arm, patient- and assessor-blinded trial will be conducted to compare the efficacy of two true EA groups (opposing EA and operated side EA) with a sham EA group (Fig. 1).

**Fig. 1 Fig1:**
[figure not shown]
The flow diagram is intended to depict the passage of participants through this RCT

The study will be sequentially conducted as follows: 114 patients in Guanghua Hospital, Shanghai University of Traditional Chinese Medicine with osteoarthritis are included (surgical contraindications are excluded); after admission, unilateral TKA will be performed as scheduled. A day before the surgery, the eligible patients will be assessed at baseline and their consent will be obtained in writing. Patients will then be randomly assigned (on a 1:1:1 ratio) to the opposing EA group, the operated side EA group, or the sham EA group. Random numbers will be generated by the SPSS 22.0 software and sealed in opaque envelopes. Only the operator in charge of acupuncture treatment is authorized to open the envelope to obtain the group code.

The three groups of subjects will receive interventions on three consecutive days after surgery, once every day, by a clinician with more than 3 years of experience in acupuncture intervention. The participants will be blinded to the intervention measures. The success of the visit would be evaluated during the last visit of each participant. Researchers who did not participate in the treatment and who did not know the allocation results will perform the outcome assessment. Unblinding before the completion of the study will only be allowed in the case of medical emergencies or severe adverse events (SAEs).

All patients will receive the same post-operative analgesic dose with a fentanyl patient-controlled analgesic (PCA) pump (continuous infusion rate 0.25 μg/(kg·h)). Additional analgesics will be provided as per each patient’s requirements ascertained by the visual analogue scale (VAS) score > 6, and the use of analgesics will be recorded in their case report form (CRF).

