Acupuncture from ancient Chinese medicine is a safe treatment method without serious side effects [12]. It can be used as a complementary and alternative therapy for many diseases such as dyspepsia [13], overactive bladder [14], stress urinary incontinence [15], etc. Clinically, it can also be used as a drug-free intervention to relieve post-operative pain and help reduce the use of opioid analgesics [16]. Post-operative pain control following TKA using acupuncture therapies has more potential to develop into effective treatment regimens than other alternative therapies [17]. Tedesco et al. [16] systematically evaluates and meta-analyses the drug-free interventions available as post-operative analgesia in the context of TKA. Medium-quality evidence shows that electrotherapy and acupuncture after TKA can reduce the use of opioids and delay opioid consumption. Electroacupuncture (EA) can stimulate acupoints to alleviate pain by linking up a painless weak electrical stimulation. EA not only relieves acute pain [18] but is also effective against chronic pain [19]. This may, therefore, be considered as an adjunct intervention for long-term pain relief in standard non-drug therapy. In Mikashima et al.’s study [20], acupuncture on the affected side provided an effective treatment for post-operative acute pain. And in our previous trial [21] on applying EA for post-operative pain management after TKA, the technique of sham EA was mastered. During our study, however, the researchers were concerned that acupuncture near the incision may increase the risk of post-operative infection, so we considered the treatment of opposing needling after operation.

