#### Dropout criteria

Any participant will be dropped from the study if she or he (1) cannot tolerate acupuncture after operation or cannot complete the study protocol scheduled; (2) cannot continue the acupuncture procedure because of surgical factors; (3) refuses to receive EA or sham EA treatment; (4) shows SAEs; (5) violates the protocol or refuses to follow up.

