**Fig. 2 Fig2:**
[figure not shown]
Acupoints of treatment, EA, and sham EA

Patients will stay in a relaxed and supine position before the onset of treatment. The acupuncturist will untie the elastic bandage that was fixed during the operation, so that the acupoints are exposed. The skin around the acupoints is sterilized with cotton dipped in 75% alcohol, and a sterile adhesive pad (10 mm in diameter, 5 mm thick) is pasted on each of the acupoints (Fig. 3). The sterile adhesive pad is made of a special sponge (Suzhou Medical Appliance Factory, China) with one sticky side which can be pasted on the skin. The role of the sterile rubber pad is to fix the location of acupoints and to ensure subject blinding. The participants in the three groups will receive a 30-min treatment on the first, second, and third day after operation by the same acupuncturist, three times per session. It will be difficult for them to ascertain which group they belong to.

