### Outcome measures

#### Primary outcome measurement

The main evaluation criterion is pain, which is divided into two parts.

The first part is a visual analogue scale (VAS). The assessment schedule is shown in Table 1. Independent assessors who are not involved in acupuncture treatments will perform the VAS assessments (asking subjects to indicate the intensity of pain at the most painful points while resting and walking). The 0–100 mm VAS is used to evaluate pain intensity, wherein 0 mm denotes painless and 100 mm represents the most intolerable pain [32]. It allows patients to mark their own feelings on the scale as the evaluation score of pain. In addition to evaluating resting pain at 6 h after the operation, the pain in both the resting and active state is measured immediately after treatment on the first to third days after the operation, and assessed at follow-up on the fifth, seventh, and tenth days after the operation.

**Table 1 Tab1:** Schedule of trial enrollment, interventions, and assessments

Items	Enrollment (pre-operative)	Allocation (baseline)	Treatment (post-operative)				Follow-up		
Time point (hour/day)	-1	-1	6 h	1d	2d	3d	5d	7d	10d
Treatment sessions (n)	–	–		1	2	3			
Informed consent	√								
Assessment of eligibility	√								
VAS (resting)		√	√	√	√	√	√	√	√
VAS (active)		√		√	√	√	√	√	√
Additional dose released by PCA pump					√				
HSS score		√				√			√
HAMA score		√				√			√
AROM		√				√	√	√	√
PROM		√				√	√	√	√
COK				√		√	√	√	√
Discomfort and acceptance of EA				√	√	√			
Assessment of blinding method						√			
Postoperative complications and adverse events				√	√	√			

*VAS* Visual Analogue Score, *PCA* patient controlled analgesia, *HSS* hospital for special surgery, *HAMA* Hamilton Anxiety Scale, *COK* circumference of knee, *AROM* active range of motion, *PROM* passive range of motion

The second part is to record any additional doses from the patient-controlled analgesic pump after the operation, and to evaluate it uniformly on the second day after the operation (at 24 h after the first treatment).

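### Patients are allocated the day before surgery although the arms do not differ until the day after it, so avoidable surgical losses become post-randomisation losses

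*Protocol article*

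**What the plan says.** **Timing of allocation.** Under Study design (text with Fig. 1): "A day before the surgery, the eligible patients will be assessed at baseline and their consent will be obtained in writing". The next step is "Patients will then be randomly assigned (on a 1:1:1 ratio) to the opposing EA group". Table 1 (Outcome measures) agrees: the column whose heading begins "Allocation (baseline" stands at time point -1, ahead of the 6 h post-operative column.

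**When the arms first differ.** Under Treatment protocol: "The participants in the three groups will receive a 30-min treatment on the first, second, and third day after operation by the same acupuncturist". Until then care is common to all arms; Study design states "All patients will receive the same post-operative analgesic dose with a fentanyl patient-controlled analgesic (PCA) pump".

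**Who can learn the arm.** Under Study design: "Only the operator in charge of acupuncture treatment is authorized to open the envelope to obtain the group code". No opening time is given.

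**Losses.** The Dropout criteria remove participants who, among other reasons, do not tolerate acupuncture after surgery or cannot complete the protocol (criterion 1), "cannot continue the acupuncture procedure because of surgical factors" (criterion 2), or have a severe adverse event (criterion 4). No decision-maker is named.

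**Analysis and size.** Statistical analysis states the intention-to-treat principle. Sample size gives 96 cases, a 15% dropout rate and 38 per arm.

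**The concern.** Nothing in the trial needs the arm to be known before the first session, so allocating on day -1 gains nothing that the article describes. It does place the whole operation between randomisation and treatment. A cancelled operation, a change of procedure or a complication that rules out acupuncture would then remove a randomised patient, where later allocation would simply have left that patient unrandomised.

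Two things are at stake. The first is attrition: these losses draw on the same 15% as losses during treatment and follow-up, and a patient dropped before session 1 contributes no post-treatment pain score to an intention-to-treat analysis. The second is neutrality between arms. If the envelope has been opened by the time someone decides that acupuncture cannot go ahead, that decision might depend on the arm. The arm most open to this is operated-side EA, the only one with penetrating needles in the operated leg. The Background reports that the researchers were concerned that "acupuncture near the incision may increase the risk of post-operative infection".

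**Working it through.** **Step 1: order of events**

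| Time | Event | Do the arms differ? |
|---|---|---|
| Day -1 | Consent, baseline, allocation (Study design; Table 1) | No |
| Day 0 | Unilateral TKA, common PCA regimen | No |
| 6 h | Resting VAS (Table 1) | No |
| Day 1 | First EA or sham EA session | Yes, from here |

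Everything between rows 1 and 4 can cost a randomised patient without any contribution from the assigned treatment. In addition, inclusion criterion 3 (unilateral TKA under general anaesthesia) can be confirmed only once the operation has taken place.

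**Step 2: which dropout criteria reach that interval.** Criterion 1 covers a patient who cannot complete the protocol, for instance because the operation is cancelled. Criterion 4 covers a severe adverse event at or after surgery. Criterion 2 names surgical factors. All three lead to the participant leaving the study, while Statistical analysis promises intention-to-treat. The article does not reconcile the two.

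**Step 3: the plan's own allowance.** Inputs from Sample size: 96 cases, hence 96/3 = 32 per arm; dropout 15%.

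- 32/(1 - 0.15) = 37.6, rounded up to 38 per arm; 3 × 38 = 114. The dropout step reproduces.
- Planned allowance: 114 - 96 = 18 patients.
- I take 96 as stated. The printed formula does not return it (43, 54 or 61 per arm for τ = 1, 2 or 3), but that is a separate matter and does not affect this point.

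**Step 4: illustration of the cost.** The documents give no rate of loss between allocation and session 1. Assume a rate L in addition to the 15%:

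- patients lost = 114 × L
- evaluable per arm = 38 × (1 - L) × 0.85
- per arm needed to keep 32 evaluable = 32/[(1 - L) × 0.85], rounded up

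| L (assumed) | Lost of 114 | Evaluable per arm | Needed per arm |
|---|---|---|---|
| 0 | 0 | 32.3 | 38 |
| 2% | 2.3 | 31.7 | 39 |
| 5% | 5.7 | 30.7 | 40 |
| 10% | 11.4 | 29.1 | 42 |

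If the 15% already includes surgical losses, the evaluable number stays at 32.3; the cost is then only that part of the allowance goes on losses that could have been avoided.

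**Step 5: neutrality between arms.** All three groups have a procedure on both legs, with the bandage untied and pads applied, so a wound or dressing that blocks access blocks every arm. What differs is penetration: 25-30 mm needles enter the operated leg only in operated-side EA. An arm-dependent decision is therefore possible only where the arm is known and the doubt concerns penetration. The text leaves both open and gives no rate or score from which to compute a bias.

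**The case against.** Randomising before surgery is a design choice and not an error in itself. The word used in criterion 2 suggests treatment already begun, so some of the losses it describes would occur after session 1 and would remain under any allocation time. Intention-to-treat is stated, and how patients lost before treatment enter the analysis may be settled in a full protocol or analysis plan that is not shown. These points stand and limit the weight of the finding. They do not remove it, because the article itself fixes the day of allocation, and criteria 1 and 4 clearly reach the interval before session 1.

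A reader might infer more than the documents support:

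- *That the acupuncturist, knowing the arm, decides who is dropped.* The article says who may open the envelope, but not when, and it names nobody who judges dropout. Opening it at the first session fits the text equally well.
- *That losses will concentrate in operated-side EA and bias that arm by a calculable amount.* The number of extra losses and the pain scores of those lost would both have to be invented. The 9.9 mm planning difference (46.9 - 37.0) compares opposing EA with sham EA, so it is not the effect that such a bias would distort. The infection concern is given as the motive for studying opposing needling, not as a reason for withdrawal.
- *That the 6 h VAS is spoiled as a baseline because it follows randomisation.* It precedes any difference between arms, in blinded patients on common analgesia, and is already usable as a covariate.
- *That later allocation would keep these patients in the analysis.* It would not; they would never be randomised, and other patients would take their places.

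**Conclusion.** The point holds as an avoidable weakness with a cheap remedy. Allocation on day -1 turns surgical losses into post-randomisation losses, and the dropout rule and the intention-to-treat statement are not reconciled for them. On an assumed additional loss of 2% to 10%, about 2 to 11 of 114 patients are affected, and the evaluable number falls to between 31.7 and 29.1 per arm against 32; it does not fall below 32 if the 15% already covers such losses. The possibility that feasibility is judged with the arm known follows from the missing opening time. It is a possibility only, and its effect cannot be sized from the documents.

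**What to change.** - Keep consent and baseline assessment on day -1.
- Assign the patient and open the next envelope on day 1, immediately before session 1, and only after existing staff unaware of the arm have recorded that unilateral TKA took place and that the patient remains eligible.
- Move the allocation column of Table 1 to that point.
- Reconcile the Dropout criteria with the intention-to-treat statement for patients lost after allocation.

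If allocation must stay on day -1, state that the envelope remains sealed until the same check is recorded, and that all randomised patients stay in follow-up and analysis. This protects neutrality but does not prevent the losses.

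Cost: a short amendment and one recorded check on day 1, with no added visit. A few consented patients will not be randomised. To randomise 114, 114/(1 - L) must consent, which is 117, 120 or 127 for the assumed 2%, 5% or 10%. Losses after session 1, including any that depend on the arm, remain.

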### Eligibility

#### Inclusion criteria

Subjects are eligible to participate if they meet the following criteria: (1) aged 40 to 75 years; (2) meet the Clinical Classification Criteria for Osteoarthritis of the Knee as recommended by the American College of Rheumatology; (3) undergoing unilateral TKA under general anesthesia during hospitalization without surgical contraindications; (4) American Society of Anesthesiologists (ASA) grade I or II [29].

#### Exclusion criteria

Participants will be excluded if they are experiencing or have a history of the following: (1) acupuncture cannot be performed because of skin lesions at acupoints; (2) lower extremity sensory disturbance or abnormality; (3) severe arrhythmias, heart failure, chronic obstructive pulmonary disease, epilepsy, mental disorders; (4) received acupuncture treatment in the past 1 month.

#### Dropout criteria

Any participant will be dropped from the study if she or he (1) cannot tolerate acupuncture after operation or cannot complete the study protocol scheduled; (2) cannot continue the acupuncture procedure because of surgical factors; (3) refuses to receive EA or sham EA treatment; (4) shows SAEs; (5) violates the protocol or refuses to follow up.

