**Methods/design:**

This is a protocol for a randomized controlled patient- and assessor-blinded trial with three parallel arms (A, opposing EA; B, operated side EA; C, sham EA). *Yinlingquan* (SP9), *Yanglingquan* (GB34), *Futu* (ST32), and *Zusanli* (ST36) acupoints are selected for all three groups. In group A, the healthy side will be treated with EA, while the operated side will be administered sham EA. In group B, the operated side will be treated with EA while on the healthy side sham EA will be used. For group C, sham EA will be used on both sides. All patients in the three groups will receive treatment once a day for 3 days. The post-operative pain measured using a visual analogue scale score (including pain while resting and being active) and the additional dose of the patient-controlled analgesic pump after operation will be recorded as the primary outcomes. Secondary outcomes such as knee function and swelling, range of motion (including active and passive range of motion), post-operative anxiety, and acupuncture tolerance will also be assessed.

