### Statistical analysis

The data in this study will be analyzed using the Statistical Package for Social Science software (SPSS version 22.0, IBM Corp, New York). After data collection, statistical analysis will be performed by a special statistician. Data analysis will be based on the intention-to-treat (ITT) principle [42], considering significance levels < 0.05 as statistically significant.

Continuous data will be represented by mean, standard deviation, median, and interquartile ranges and the categorical data by percentages.

According to whether the data are normally distributed, the analysis of baseline will be performed using a *t*-test or a Wilcoxon rank sum test for continuous data and a chi-squared test or Fisher’s exact test for categorical data. Comparisons among the three groups will be analyzed by one-way analysis of variance (ANOVA) [43]. When the distribution is not normal, nonparametric tests will be used. Thus, the primary outcome will be assessed using a one-way, repeated-measures ANOVA to test the influence of the time, the group, and the time*group interaction on pain. Comparisons of categorical data among groups will be tested by the chi-square test or the Mann Whitney U-test.

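### The dropout rule takes randomised patients out of the study for treatment-related reasons, which conflicts with the intention-to-treat analysis and can bias the arm comparison

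*Protocol article*

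**What the plan says.** Four parts of the protocol article bear on this point.

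- **Study design.** "A day before the surgery, the eligible patients will be assessed at baseline and their consent will be obtained in writing". The next sentence reads "Patients will then be randomly assigned (on a 1:1:1 ratio) to the opposing EA group" and names the other two arms. Table 1 also places allocation on day −1. Treatment is given on days 1, 2 and 3 after surgery.
- **Dropout criteria.** Item 1: "Any participant will be dropped from the study if she or he (1) cannot tolerate acupuncture after operation"; the same item also covers patients who do not finish the planned schedule. Item 2 covers surgical factors that prevent acupuncture from continuing. Items 3 to 5: "3) refuses to receive EA or sham EA treatment; (4) shows SAEs; (5) violates the protocol or refuses to follow up".
- **Statistical analysis.** "Data analysis will be based on the intention-to-treat (ITT) principle". The primary outcome is to be tested with a repeated-measures ANOVA.
- **Sample size.** 96 cases are raised to 38 per group to allow for 15% dropout.

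The abstract adds tolerance to the outcomes: "post-operative anxiety, and acupuncture tolerance will also be assessed". It also names efficacy and safety as the aims.

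**The concern.** Intention to treat keeps each randomised patient in the allocated arm whatever the adherence, tolerance or adverse events. The dropout rule makes those same events grounds for leaving the study, not only for leaving treatment. Anyone who applies it literally stops assessing the patient, and no later analysis plan can recover measurements that were never taken.

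The reasons for removal may well depend on the arm. True EA puts needles 25–30 mm into the tissue and passes current, while sham EA neither penetrates the skin nor carries current. The Discussion itself expects needling on the operated side to carry more infection risk and to be less acceptable to patients. If patients leave at different rates or for different reasons across arms, those who remain are no longer the groups that randomisation made comparable.

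**Working it through.** **1. The planned dropout figure reproduces.** From Sample size: 96 cases in three groups is 96/3 = 32 per group. With 15% dropout, 32/(1 − 0.15) = 37.6, rounded up to 38, and 3 × 38 = 114, as stated. The trial is therefore sized as if dropouts contribute nothing: 15% of 114 is about 17 patients, leaving 114 × 0.85 = 96.9. (Whether 96 follows from the printed formula is a separate matter and is not used here.)

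**2. What a dropped patient loses under Table 1.**

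| Assessment | Scheduled after surgery | Lost if dropped on days 1–3 |
|---|---|---|
| VAS | 6 h (resting only), days 1, 2, 3, 5, 7, 10 | Days 5, 7, 10, and any remaining day 1–3 value |
| Active and passive range of motion | Days 3, 5, 7, 10 | Days 5, 7, 10, and day 3 if dropped before it |
| HSS, HAMA | Days 3, 10 | Day 10, and day 3 if dropped before it |
| Discomfort and acceptance; complications and AEs | Days 1, 2, 3 | Only what remains of days 1–3 |
| Additional PCA dose | Day 2 | Only if dropped before that reading |

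A repeated-measures ANOVA in its classical form uses only complete series. A patient without days 5–10 could then fall out of the primary test altogether, including the values already recorded.

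**3. Size of a possible bias.** Let q be the fraction removed from an arm and D the mean VAS of removed patients minus that of retained patients. The full-arm mean is (1 − q) × retained mean + q × (retained mean + D) = retained mean + qD, so the retained mean lies qD below it. For EA against sham, the bias in the difference is −(q_EA × D_EA − q_sham × D_sham).

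The planning difference is 46.9 − 37.0 = 9.9 mm (opposing EA against sham, Sample size). The values of q and D below are **assumptions**; the document gives neither by arm. D is the same in both arms.

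| Removed, EA vs sham | D = 10 mm | D = 20 mm | D = 30 mm |
|---|---|---|---|
| 15% vs 15% | 0 | 0 | 0 |
| 15% vs 5% | 1 mm (10%) | 2 mm (20%) | 3 mm (30%) |
| 25% vs 5% | 2 mm (20%) | 4 mm (40%) | 6 mm (61%) |

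Percentages are of 9.9 mm; for example, (0.15 − 0.05) × 30 = 3 mm and 3/9.9 = 30%. In these rows the bias favours EA. If sham lost more patients, the same sizes would apply with the opposite sign.

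**The case against.** The best defence is that the dropout rule does not say that data already collected are discarded, and that the only statement on the analysis population is intention to treat. Dropped patients keep their allocation and their earlier values. The handling of missing values is commonly left to an analysis plan that is not shown. This stands in part: an intention-to-treat analysis with missing values is possible, so the document does not make one impossible. It does not remove the conflict, because the rule ends participation in the study and nothing in the article says that assessments continue.

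A reader might infer more than the text supports:

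- **That the rule flatters real EA.** This needs removal rates or pain gaps that differ by arm in a known direction. The article applies one 15% allowance throughout. Sham patients leaving with unrelieved pain would push the other way, and surgical factors need not depend on arm.
- **That the bias is 16–48% of the planning difference.** Losing 6 of 38 with a 10–30 mm gap shifts one arm's mean by 6/38 × 10 = 1.6 mm to 6/38 × 30 = 4.7 mm. If sham also loses 6 of 38 with the same gap, it shifts equally and the net bias is 0.
- **That harm is understated.** The SAE that triggers removal has already occurred and can be recorded, and the intolerance is itself a tolerance finding. Table 1 schedules AE recording on days 1–3 only, so at most the rest of those days is lost.
- **That every listed reason breaks intention to treat.** Refusal of follow-up is ordinary loss to follow-up and does not.

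**Conclusion.** The conflict is real and lies in stated text: the Dropout criteria remove randomised patients for reasons that an intention-to-treat analysis must disregard, and the Sample size section treats those patients as lost. Following the rule causes avoidable missing data on the VAS and the rehabilitation outcomes.

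It can bias the arm comparison; the document does not show that it will, or in which direction. The contrast between penetrating EA with current and non-penetrating sham makes unequal removal plausible, no more. The 1–3 mm figure rests wholly on an assumed 15% against 5% removal and an assumed 10–30 mm gap common to both arms.

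**What to change.** Reconcile the Dropout criteria with the Statistical analysis section:

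1. Make the listed reasons, other than refusal of follow-up, grounds for discontinuing study treatment only. When needling stops is not in question and no change to it is proposed.
2. State that these patients stay in all scheduled assessments through day 10 unless they withdraw consent. Keep refusal of follow-up as ordinary loss to follow-up.
3. Analyse all randomised patients in their allocated arm with a method that does not need complete series; a mixed model is one example.
4. Report discontinuations by arm and reason, so that any imbalance can be seen.

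This takes a short amendment and a few extra assessments at visits already in Table 1. The number randomised stays at 114.
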